### Trial interventions

#### Intervention plus usual care group

Intervention group patients will be treated with additional secondary prevention medications, unless there are clinical contraindications, prior to referral to a specialist clinic. Treatment will comprise of dual anti-platelets, blood-pressure lowering medication, and simvastatin 40 mg. All patients will then be referred to a specialist clinic as per NICE guidelines (with the degree of urgency dictated by the ABCD2 score) [6].

#### Dual anti-platelets

In patients not already on anti-platelet or anti-coagulant therapy, aspirin 300 mg once daily will be started for the first 2 weeks or until reduced by a specialist. Dipyridamole MR 200 mg twice daily will be started in patients not already on anti-platelet or anti-coagulation therapy other than aspirin. Any anti-coagulation or anti-platelet agents the patient is already taking will be continued.

#### Blood-pressure lowering medication

Unless BP is below 130 mmHg systolic on either of two readings taken one minute apart or the patient is already taking all three of a thiazide diuretic, ACE-inhibitor and calcium channel blocker, then one of these three classes of medication will be initiated according to the PCP’s clinical choice. If the patient is already taking all three drug classes, one agent should have its dose increased within its licensed dosage according to the PCP’s clinical choice.

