#### Exclusion criteria

Patients will be excluded if:

• The PCP considers that immediate emergency admission is required for any reason. This will include patients where symptoms have not substantially resolved by the time they see the PCP. PCPs will record reasons for exclusion.

• The patient has experienced a TIA or stroke within the previous month.

• The PCP is not in equipoise.

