#### Initial presentation in daytime general practice

Participating general practices have a lead GP, who coordinates recruitment into the trial. Patients may present with suspected TIA at any time to a GP in the practice, who may be assisted in aspects of patient care by a practice nurse. When a patient presents, the clinician will take a history, examine the patient and come to an initial diagnosis of possible or probable TIA or minor stroke as per usual practice, and then:

1. Inform the patient of the suspected diagnosis as per usual practice.

2. Discuss the information sheet with the patient.

3. Confirm the inclusion and exclusion criteria.

The patient will be given time to consider the information and to ask questions. The clinician will then:

4. Obtain informed consent if the patient is willing to take part.

5. Record clinical features and whether TIA is probable or possible.

For patients diagnosed with probable TIA or minor stroke, the clinician will also undertake the following:

6. Consider the relative indications and contraindications to therapy.

7. Take the patient’s blood pressure.

8. Record any current medication.

9. Randomise the patient to the intervention or control arm.

10. Prescribe and dispense the allocated medication.

11. Ask the patient to bring their medication to the specialist clinic.

Finally, all patients will be referred to the TIA clinic with urgency determined by local guidelines. The GP will also arrange any additional appropriate follow-up consistent with usual practice.

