#### Specialist clinic

All patients will have been referred to the TIA clinic as per local protocol consistent with NICE guidelines and therefore will usually be reviewed within 7 days of symptom onset (or within 24 hours for higher risk TIAs). Specialists will manage patients according to their usual practice, including changing any medication started by the primary care physician. In addition, the specialist doctor, supported by nursing staff, willrecord clinical features, ABCD2 score, blood pressure, final diagnosis, current medication, persistence with primary care initiated medication and changes to medication.

Additionally, the research nurse will check the patient’s hospital record for a final diagnosis when this is available if it is not confirmed during the initial TIA clinic attendance; the research nurse will also obtain an up-to-date medication list from the patient’s GP record if this has not been provided at initial presentation.

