#### Adverse events

Unplanned hospitalisation and falls between entry into the trial and the first specialist appointment will be reported as possible adverse events.GP contacts will be recorded. If Read codes suggest treatment has led to additional GP contacts, the research team will retrospectively analyse the GP record for further details.

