There is currently no evidence that rapid administration of statin treatment is beneficial. The FASTER study investigated treatment with simvastatin 40 mg once daily versus a placebo in 392 patients within 24 hours of a stroke or TIA and failed to demonstrate whether this was either harmful or beneficial (the absolute risk increase of stroke within 90 days was 3.3%; the 95% confidence interval was −2.3% to 8.9%; *P*=0.25) [12]. However, there is evidence that statin treatment reduces the incidence of recurrent stroke in the long term in people who have experienced a stroke or TIA [28-30] and statin treatment is recommended for all patients who experience ischaemic stroke/TIA [6].

Approximately 50% of people referred to TIA clinics have not experienced a TIA or minor stroke [31]. Common alternate diagnoses include migraine, faints, vertigo and epilepsy [32]. It is therefore likely that this trial will increase the number of people who are given blood pressure treatment, statin therapy and anti-platelet agents for the brief period (usually less than 7 days) before they are reviewed by the specialist clinic. However, all these agents are commonly used in primary care to prevent cardiovascular disease, and it is unlikely that 1 to 7 days of unnecessary treatment will cause substantial harm – indeed, since clinicians use cardiovascular risk factors to assess the likelihood of TIA or minor stroke, many patients with alternative diagnoses may benefit from these drugs and the focus on their cardiovascular risk that a suspected diagnosis brings. Significant adverse events that occur prior to specialist clinic attendance will, however, be recorded.

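### The 130 mmHg systolic floor applies to starting a blood-pressure drug but not to the dose increase for patients already on all three classes

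*Protocol article*

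**What the plan says.** The rule is in the protocol article, section Blood-pressure lowering medication, and has two sentences.

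- The first directs the primary care physician (PCP) to start one of three classes (thiazide, ACE-inhibitor, calcium channel blocker), with two exceptions joined by *or*. One is a low reading: "Unless BP is below 130 mmHg systolic on either of two readings taken one minute apart". The other is that the patient already takes all three classes.
- The second deals with patients under that other exception: "If the patient is already taking all three drug classes, one agent should have its dose increased within its licensed dosage". The PCP chooses the agent.

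Three more general provisions also bear on the decision.

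- Intervention plus usual care group: "Intervention group patients will be treated with additional secondary prevention medications, unless there are clinical contraindications".
- The entry procedures for general practice, out-of-hours practice and the emergency department each include this step before randomisation: "Consider the relative indications and contraindications to therapy".
- Exclusion criteria bar a patient if "The PCP is not in equipoise".

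**The concern.** The floor is attached to one action, starting a class. The second sentence prescribes a different action, raising a dose, and limits it only by the licensed dosage. The two sentences do not contradict each other, but the floor is missing from the second.

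The result is an unexplained reversal. The patient already on the most antihypertensive treatment, with a reading the rule treats as too low for adding a drug, is directed to further lowering before any specialist has seen them. The article gives no reason for treating the two patients differently.

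Two things are at stake.

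- **Safety.** The events the trial reports as possible adverse events are "Unplanned hospitalisation and falls between entry into the trial and the first specialist appointment", and this is the period in which the extra dose would be taken.
- **Adherence.** The pilot counts patients who received their allocated intervention (section Recruitment rate). A PCP who sensibly withholds the increase below 130 mmHg has, on the literal text, not delivered it.

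**Working it through.** There is no figure of the plan's own to reproduce. The check is to enumerate the rule and to look for a threshold elsewhere.

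**Inputs** (section Blood-pressure lowering medication): whether either systolic reading is below 130 mmHg, and whether the patient already takes all three classes. Two binary inputs give 2 × 2 = 4 combinations.

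| Current drugs | Readings | Rule as written | Floor applied to both actions |
|---|---|---|---|
| Fewer than three classes | Both ≥130 | Start a class | Start a class |
| Fewer than three classes | Either <130 | No new class | No new class |
| All three classes | Both ≥130 | Increase one dose | Increase one dose |
| All three classes | Either <130 | **Increase one dose** | **No change** |

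**The fourth row, step by step.**

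1. The patient takes all three classes, so the first sentence does not apply, whatever the pressure.
2. The low reading is a second, separate reason why that sentence does not apply. Its only effect there is to block the start of a new class.
3. The second sentence applies, because its one entry condition (all three classes) is met. Its only limit is the licensed dosage.
4. The instruction is therefore to increase a dose.

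**Could the floor be inferred from the first sentence?** Not from its structure. Patients under the all-three-classes exception are actively treated by the second sentence, so meeting an exception does not by itself mean that blood-pressure treatment is left alone.

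**Is there a floor elsewhere?** No other section gives a blood-pressure threshold for treatment. The contraindication clause, the pre-randomisation step and the equipoise exclusion contain no blood-pressure value. All three apply equally to starting a class, where a numerical floor was written in addition to them.

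**The case against.** The best case against has four parts.

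1. **The floor may be implied.** The second sentence can be read as taking up only the patient who has run out of classes to add, so that anyone with a low reading has already been held back. This is a plausible account of intent. It is not what the text says, because the first sentence restricts only initiation. If it was the intent, adding the clause simply records it.
2. **Clinical judgement covers the case.** The PCP considers contraindications, measures blood pressure and records medication before randomising, and need not randomise without equipoise. The dose increase is also worded as *should*, where initiation is *will*. These safeguards are real and make an unwise increase less likely. They still set no floor, and nothing in the article makes a reading just under 130 mmHg a contraindication. The PCP's choice most naturally concerns which agent to raise.
3. **The article condenses a longer protocol.** The full document may word the rule differently, and this cannot be checked. But the article does not merely omit detail here: it states the rule with a threshold, a number of readings and an interval between them, and that stated rule has the gap.
4. **The consequence is slight.** This stands. Few or no patients may be affected, and the article gives no evidence that one licensed dose step just below 130 mmHg does harm. Treatment before the clinic visit is given "for the brief period (usually less than 7 days) before they are reviewed by the specialist clinic", specialists then manage as usual, "including changing any medication started by the primary care physician", and hospital admissions are reviewed by an independent expert. These facts limit the severity of the point without removing the gap.

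**Conclusion.** The concern holds as a minor safety and consistency point. As written, the 130 mmHg floor does not reach the dose-increase instruction.

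One of four combinations is affected: an intervention-arm patient on all three classes with either reading below 130 mmHg. The article does not say how many such patients to expect. Among about 100 planned trial patients the number is probably small and may be zero. Exposure is one dose step, usually for under 7 days. No estimate, analysis or sample size depends on it.

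The conclusion rests on the literal wording of the published rule. It assumes neither that the authors intended the difference nor that the full protocol repeats it.

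**What to change.** In the second sentence of the rule, after the condition that the patient takes all three classes, insert: *and systolic BP is 130 mmHg or above on both readings*. This is the exact complement of below 130 on either reading, so only the fourth row of the table changes.

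The section Trial status gives recruitment as closed on 31 December 2012, so the wording cannot affect pilot patients and should be carried into the main trial protocol. If the sponsor wants up-titration below the floor, the protocol should say so and give the reason.

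The cost is one clause. No new case report form item is needed, because blood pressure is already taken and current medication recorded at entry. The only downside is that a few intervention patients on three agents with a reading below 130 mmHg would receive no blood-pressure change.

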#### Simvastatin 40 mg once daily

Simvastatin 40 mg daily will be started unless the patient is already on statin treatment of equivalent intensity.

Clinicians should check liver function or renal function when starting statins or blood-pressure lowering medication according to their usual practice, but results are not mandatory prior to initiating treatment.

#### Usual care group

This is the control group. If patients are not already on anti-platelet therapy, a loading dose of aspirin will be administered (300 mg daily) and patients will be referred to a specialist clinic as per NICE guidelines (with the degree of urgency dictated by the ABCD2 score) [6]. All patients will be instructed to continue with their usual medication unless a clinician makes a specific decision to alter it for any reason.

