### Summary of procedures and staffroles

Throughout the trial, the primary care physicians will be instructed to follow usual practice, which should be consistent with the 2008 NICE stroke guidelines [6]. All patients with suspected TIA or minor stroke should be continued on their anti-platelet treatment or started on aspirin 300 mg daily unless there are contraindications and referred to a specialist clinic (with the degree of urgency dictated by the ABCD2 score) [6]. The intervention group will receive treatment additional to this usual care.

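### For patients taking an anti-coagulant but no anti-platelet, the aspirin start rule differs between arms, so for them the anti-platelet part of the intervention is not added to usual care

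*Protocol article*

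**What the plan says.** All references are to the protocol article.

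- **Control arm (Usual care group).** Aspirin depends on anti-platelet use only: "If patients are not already on anti-platelet therapy, a loading dose of aspirin will be administered (300 mg daily". Existing drugs go on: "All patients will be instructed to continue with their usual medication unless a clinician makes a specific decision to alter it for any reason".
- **Intervention arm (Dual anti-platelets).** Aspirin depends on anti-coagulant use as well: "In patients not already on anti-platelet or anti-coagulant therapy, aspirin 300 mg once daily will be started for the first 2 weeks". Dipyridamole has its own condition: "Dipyridamole MR 200 mg twice daily will be started in patients not already on anti-platelet or anti-coagulation therapy other than aspirin". Existing agents stay: "Any anti-coagulation or anti-platelet agents the patient is already taking will be continued".
- **Both arms (Summary of procedures and staff roles).** Patients with a suspected event "should be continued on their anti-platelet treatment or started on aspirin 300 mg daily unless there are contraindications". The section then defines the contrast: "The intervention group will receive treatment additional to this usual care".
- **Eligibility (Exclusion criteria).** The three exclusions are need for emergency admission, a TIA or stroke in the previous month, and a physician not in equipoise. Anti-coagulant use is not among them, and the instruction to continue existing anti-coagulants shows that such patients are expected.

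**The concern.** The design is usual care against usual care plus extra drugs. That requires the usual-care part to be the same in both arms, so that the arms differ only by what is added. If a background drug is started under one rule in control and a narrower rule in intervention, some patients differ between arms in a way that is not the intervention.

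Aspirin bears directly on the outcomes. Major bleeding and haemorrhagic stroke are listed secondary outcomes, and the Discussion says that anti-platelet agents lower stroke risk and raise bleeding risk. The pilot also has to count receipt of allocated treatment and contamination, and both counts need one definition of usual care. The pilot exists to design a main trial, so an unreconciled rule could be carried forward.

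**Working it through.** No sample size, power or error rate in the protocol depends on this point, so there is no stated figure to reproduce. The check applies the printed rules to every baseline state.

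**Rules as written**

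- Intervention, aspirin: start if on no anti-platelet and no anti-coagulant.
- Intervention, dipyridamole: start if on no anti-coagulant and no anti-platelet other than aspirin.
- Control, aspirin: start if on no anti-platelet.
- Contrast = (intervention aspirin + intervention dipyridamole) − control aspirin, counting newly started agents.

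| Anti-coagulant | Aspirin | Other anti-platelet | Intervention: aspirin + dipyridamole | Control: aspirin | Contrast |
|---|---|---|---|---|---|
| no | no | no | 1 + 1 | 1 | +1 |
| no | yes | no | 0 + 1 | 0 | +1 |
| no | no | yes | 0 + 0 | 0 | 0 |
| no | yes | yes | 0 + 0 | 0 | 0 |
| **yes** | **no** | **no** | **0 + 0** | **1** | **−1** |
| yes | yes | no | 0 + 0 | 0 | 0 |
| yes | no | yes | 0 + 0 | 0 | 0 |
| yes | yes | yes | 0 + 0 | 0 | 0 |

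The contrast is negative in exactly one of the eight states: anti-coagulant without anti-platelet. In every other state the intervention arm adds one agent or none, and withholds nothing that control starts. The blood-pressure and simvastatin rules do not refer to anti-coagulants, so those components are still added in the affected state.

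**Number affected**

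The protocol gives no share of patients on an anti-coagulant alone. The 2% to 15% below is an assumption for illustration. The trial size of 100 is from Recruitment; 50 per arm assumes roughly equal arms.

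- 2%: 0.02 × 100 = 2 patients; 0.02 × 50 = 1 per arm.
- 5%: 5 patients; 2.5 per arm.
- 10%: 10 patients; 5 per arm.
- 15%: 15 patients; 7.5 per arm.

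The minimisation factors are catchment area, clinic type and ABCD2 score, so the split of these few patients between arms is left to chance.

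**The case against.** The strongest reply is that the protocol already leaves room to withhold aspirin. The usual-care statement in the Summary carries a contraindication proviso. The procedure lists for all three settings require the clinician to weigh contraindications and record current medication before randomising. A physician not in equipoise need not enter the patient. On this reading aspirin would often be withheld from an anti-coagulated control patient, and an article that condenses a fuller protocol need not say more.

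Much of this stands as a description of practice, but it does not remove the conflict. The control-arm rule itself has no proviso, and neither the proviso nor the procedure lists name anti-coagulation. The intervention-arm rule makes it a fixed condition. One arm therefore has an explicit rule and the other relies on individual judgement, exercised by a clinician who randomises and then prescribes, and so knows the allocation. Nor is this a matter of omitted detail: both rules are printed, and they differ.

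Four stronger readings are tempting and are not supported:

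- *All anti-coagulated patients are affected.* Those also on an anti-platelet start no new anti-platelet in either arm; their contrast is nil.
- *The intervention arm as a whole is not usual care plus.* The failure is confined to one baseline state and one drug component.
- *The pilot's stroke or bleeding comparison is biased by a material amount.* The logistic regression is stated for the main trial; the pilot is to summarise by group and report feasibility, a preliminary event rate and adverse events. The protocol gives neither the size of the affected group nor its bleeding risk.
- *The arms specify different aspirin durations.* The intervention arm states a duration and the control arm is silent. Specialists may change any medication, usually within 7 days of symptom onset, so the wording would usually be overtaken by clinic review.

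**Conclusion.** The inconsistency is real and narrow. Read as printed, Dual anti-platelets conflicts with Usual care group, and with the description of the intervention in the Summary, for patients on an anti-coagulant and no anti-platelet. For them the anti-platelet contrast is −1 instead of 0 or +1. This follows from the wording alone and needs no assumption about numbers.

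The number of patients concerned does need one. The assumed 2% to 15% gives 2 to 15 of 100, with no figure in the protocol to narrow it, and the group is probably small. The effect on any estimate cannot be quantified, and the contraindication proviso would reduce it to an unknown degree. The point matters mainly for the definition of usual care, for the receipt and contamination counts, for reading any bleeds in this group, and for what passes into the main trial. Nothing here says which aspirin rule is clinically right.

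**What to change.** **Main-trial protocol.** Reconcile Dual anti-platelets, Usual care group, and Summary of procedures and staff roles. State one usual-care aspirin rule, including how anti-coagulated patients are handled, and apply it identically to both arms, so that the arms differ only by the added drugs. The choice of rule belongs to the clinical investigators. Stating the aspirin duration once for both arms can be done in the same edit.

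**Pilot report.** Recruitment closed on 31 December 2012, so treatment in the pilot cannot be changed. Within the baseline-therapy sub-group already planned under Analysis, tabulate by arm and baseline anti-coagulant use (separating patients with and without an anti-platelet) the aspirin actually given and the major bleeds. Present these as counts, without a test.

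**Cost.** A wording change in the next protocol and one table in the pilot report. Current medication is already recorded at entry and again at the specialist clinic, so no extra patients, visits or data items should be needed.
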